### Evaluation of impact on racial inequities in sepsis care (Aim 3)

We will evaluate the impact of the intervention on racial inequities in three sepsis-related outcomes: a) early identification (time to antibiotic), b) in-hospital mortality, and c) 30-day hospital readmission, using comparative interrupted times series (ITS) analysis. *Time to Antibiotics*: We will use hospital EHR data to determine the difference in mean time from hospital arrival to first antibiotic administration for all AA/B patients and NHW patients and between LatinX and NHW patients respectively presenting with sepsis. This value will be calculated quarterly. We will use *t-tests* to measure statistically significant differences between AA/B and NHW patients, and LatinX and NHW patients. A clinically meaningful difference in mean time to antibiotic would be 30 min [88–93]. *In-Hospital Mortality:* We will use hospital EHR data to determine the difference in quarterly in-hospital mortality rate by 30 days for AA/B and NHW patients and LatinX and NHW patients admitted for sepsis. Rates will be standardized by age and sex [94]. At each time point, we will use *t-tests* to measure statistically significant differences between AA/B and NHW patients, and LatinX and NHW patients. Currently, the rates of in-hospital mortality for AA/B are nearly double those of NHWs, and although the overall rates of sepsis mortality have remained relatively stable over the past decade, this gap has persisted [38]. A clinically meaningful difference in rates of in-hospital mortality would be greater than 1%. *30-Day Hospital Readmission:* We will use hospital EHR data to determine the difference in quarterly 30-day, same-hospital, all-cause readmission rate for AA/B patients and NHW patients, and LatinX and NHW patients with an index hospitalization for sepsis. Rates will be standardized by age and sex. We will use *t-tests* to measure statistically significant difference between AA/B and NHW patients, and LatinX and NHW patients. A clinically meaningful difference in rates of 30-day readmission would be 5% [7]. *Sepsis Case Identification:* We will identify hospital admissions for sepsis using validated International Classification of Diseases, Ninth Revision, Clinical Modification (ICD-9-CM) diagnosis procedure codes for infection and organ failure. This strategy [4], known as the Dombrovskiy strategy, is more sensitive than methods that use only ICD-9-CM codes for sepsis [95] and will allow the investigative team to include patients with sepsis that may have otherwise been missed by chart review that would still be eligible for evidence-based practices. For each health system, we expect to be able to observe at least 140 AA/B patients with sepsis each year (within a sample of MCCN member health systems, average inpatient volumes are over 19,000, patient population is approximately 12% AA/B, and nationally, sepsis is present in 6% of adult hospitalizations) [4]; therefore, we anticipate being able to track enough cases within each health system for each clinical outcome at each quarter.

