#### Evidence of structural racism in sepsis care and outcomes

AA/B and LatinX populations have higher rates of complications leading to sepsis [37], deviations from standard sepsis care, higher in-hospital mortality, and higher all-cause and sepsis readmissions compared with NHW populations [7, 10]. Sepsis-related mortality for AA/B patients is nearly double that for NHWs across all age groups (rate ratio = 1.78) nationally [38]. AA/B patients are twice as likely to die from severe infections driven by antibiotic resistance as compared to NHWs; many of these are sepsis deaths [21]. Racial inequities are observed at all stages in the care pathway for patients at risk of sepsis. At the level of primary prevention, AA/B and LatinX people experience higher levels of chronic comorbidities, and lower rates of access to primary care [17, 19, 20], including vaccination (which reduces incidence of sepsis) [16]. At the level of care seeking, AA/B and LatinX patients have well-justified mistrust in engaging with the health care system [14], demonstrate lower awareness of sepsis [39], receive less timely and accurate triage [18, 40], and receive lower intensity use of diagnostics and treatment (e.g., less likely to receive ICU care, longer length of stay, less frequent referral for follow-up care). AA/B patients are more likely to experience poverty and lack of insurance [8], both of which are associated with poorer care and outcomes along the care continuum, although many of these inequities persist when controlling for insurance status [41–43]. Finally, AA/B patients experience implicit bias at the provider and health care system levels; however, currently no studies examine the role of implicit bias in sepsis care [44–46]. Sepsis Alliance, the nation’s first and leading sepsis organization, has emphasized the urgency of addressing racial inequities in sepsis care, prioritizing this issue in its mission and issuing a national call to action [21].

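### Time to antibiotic is a mean over all sepsis patients, but never-treated patients have no value, so the stated mean describes treated patients only and the racial gap can be distorted in either direction

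*Protocol article*

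**What the plan says.** The Aim 3 section of the protocol article fixes three things about this outcome.

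- **Summary and population.** The outcome is "the difference in mean time from hospital arrival to first antibiotic administration for all AA/B patients and NHW patients", with a parallel LatinX comparison, for patients presenting with sepsis. On frequency the text says "This value will be calculated quarterly". Groups are compared by t-test, and the benchmark is explicit: "A clinically meaningful difference in mean time to antibiotic would be 30 min".
- **Case finding.** Admissions are identified from "diagnosis procedure codes for infection and organ failure". The stated purpose of this sensitive strategy is to "include patients with sepsis that may have otherwise been missed by chart review that would still be eligible for evidence-based practices". Receipt of an antibiotic is not part of the case definition.
- **Model.** The Analytic approach section uses segmented regression in a mixed model, with a linear probability model for all analyses. It describes no censoring or time-to-event element.

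The article presents time to antibiotic as its measure of early identification. It gives no baseline time, no standard deviation and no share of patients who never receive an antibiotic.

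**The concern.** The summary does not fit the population. An admission coded for infection and organ failure, but with no antibiotic, is one of the patients the text says it covers, yet it contributes no time. Followed as written, the calculation yields a mean conditional on treatment. Complete failure to identify is the worst result on an early-identification measure, and it is the one result the mean cannot show.

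Two things are at stake. First, if non-receipt is more common in one group, the measured gap at baseline leaves that part of the inequity out. Second, the intervention aims to change care, so it may change who has a time at all. A change in the make-up of the treated group that coincides with launch would enter the interrupted time series as if it were a change in speed.

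**Working it through.** **1. The plan's own count.** The article says "we expect to be able to observe at least 140 AA/B patients with sepsis each year" per system. Its inputs are 19,000 admissions, 12% AA/B and 6% sepsis: 19,000 × 0.12 × 0.06 = 136.8. This agrees with 140, since the volume is given as over 19,000. Per quarter, 140 / 4 = 35 AA/B patients per system.

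**2. What the mean leaves out at baseline.** Nothing in the article sizes non-receipt, so the inputs here are assumptions: treated times lognormal with median 2.5 h and log-SD 0.8, identical in both groups. The mean among treated patients is 2.5 × exp(0.8²/2) = 3.44 h in each group, so the measured gap is 0 min. Now give never-treated patients a limit value H. The capped mean among the treated is 3.43 h at H = 24 h and 3.32 h at H = 12 h.

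Hidden gap = (AA/B non-receipt − NHW non-receipt) × (H − capped mean) × 60 min.

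| Excess non-receipt | H = 24 h | H = 12 h |
|---|---|---|
| 1 point | 12 min | 5 min |
| 2 points | 25 min | 10 min |
| 3 points | 37 min | 16 min |

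For example, 0.02 × (24 − 3.43) × 60 = 24.7 min and 0.02 × (12 − 3.32) × 60 = 10.4 min.

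**3. Which way the measured gap moves when untreated patients begin to be treated.** If a share u of a group gains a value at mean time L, and the already-treated mean is m, the group's observed mean shifts by u × (L − m). The gap therefore changes by the AA/B shift minus the NHW shift. Assume treated means of 210 min (AA/B) and 180 min (NHW), so the gap before is 30 min, and that all untreated patients become treated.

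| L | Gap after; untreated 7% AA/B, 2% NHW | Gap after; untreated 5% in both |
|---|---|---|
| 60 min | 21.9 min | 28.5 min |
| 360 min | 36.9 min | 28.5 min |
| 720 min | 54.9 min | 28.5 min |

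For L = 720: (0.93 × 210 + 0.07 × 720) − (0.98 × 180 + 0.02 × 720) = 245.7 − 190.8 = 54.9. The gap widens only when newly treated patients are dosed later than the current mean and the shift is larger in AA/B than in NHW patients. In the 720-min case, with log-SD 0.8 again assumed, a mean over all cases capped at 24 h falls from a gap of about 90 min to about 54 min, so the two summaries disagree on direction.

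**4. A milder case, on the assumptions of step 2.** AA/B non-receipt falls from 4% to 1%, with new doses at 6, 8 or 12 h. The AA/B mean shifts by (0.03 / 0.99) × (L − 3.43) × 60 = +4.7, +8.3 or +15.6 min. These are shifts in one group. If NHW non-receipt falls proportionally, from 2% to 0.5%, the NHW shift is (0.015 / 0.995) × (L − 3.43) × 60 = +2.3, +4.1 or +7.8 min. The gap then changes by +2.4, +4.2 or +7.8 min. If both groups go from 4% to 1%, it changes by 0.

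**The case against.** **Condensed article.** How patients without an event time are handled is commonly left to the full protocol or SAP, so the lack of a handling rule is no finding. That stands. What remains is that the article commits to a mean over a population in which it is not defined for everyone.

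**Evidence for differential non-receipt.** A reader might infer that the code-based definition brings in patients whose sepsis clinicians overlooked. The text says missed by chart review, which is a rival way of finding cases; it does not say they went untreated. A reader might also infer racial differences in non-receipt from the Background statement that AA/B and LatinX patients "receive lower intensity use of diagnostics and treatment". Its examples are ICU care, length of stay and follow-up referral, and antibiotic non-receipt is not among them. Less timely triage implies later doses, which the mean does capture. Differential non-receipt is therefore a possibility, not something the article documents.

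**Direction.** It is tempting to say that reaching untreated patients will make the gap look worse. The documents do not support that as a general statement, because it needs both conditions in step 3 of the working.

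**Time series.** A non-receipt difference that is stable across quarters does not bias a level or slope change. Only a change in non-receipt does, and the article does not show that one will occur or that it will differ between changers and non-changers.

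**A capped mean as replacement.** It depends on the limit and is noisy. With 35 patients, one untreated patient set to 24 h moves a system-quarter mean by (24 − 3.43) × 60 / 35 ≈ 35 min. With 3% at the cap, the assumed SD rises from 3.1 to 4.7 h. The plan's 30 min is also stated for mean time to antibiotic, not for a capped composite. These points stand, and they argue against making the capped mean the sole outcome.

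**Conclusion.** The point holds in a limited form. The stated mean for all patients is in fact a mean among treated patients, because the case definition does not require treatment. That follows from the text without any assumption. As a consequence the baseline gap can be understated if non-receipt differs by race or ethnicity, and the measured gap can move either way if non-receipt changes after launch.

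The size is unknown. The figures of about 25 min (24 h limit) and 10 min (12 h limit) for a 2-point excess rest on an assumed time distribution, an assumed excess and a chosen limit. They show that a small difference could matter against the plan's 30 min, not that it does. This is an inexpensive improvement to an outcome definition; it does not show that the planned analysis will be biased.

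**What to change.** - State that the mean time to first antibiotic is computed among treated patients.
- Beside it, in the same segmented linear probability model, analyse the proportion of all identified cases with a first antibiotic within a prespecified measurement window. Count never-treated patients as not treated. The window is an analytic choice, not a treatment target.
- Tabulate the never-treated proportion by race/ethnicity and quarter, so that any change in who contributes to the mean is visible.
- As a sensitivity analysis, report the restricted mean to a fixed limit, with never-treated patients at the limit. Repeat it without admissions whose only coded infection is viral.

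The cost is one more reported measure and one tabulation from the EHR data already planned. The added proportion depends on the chosen window, and some coded cases will rightly have received no antibiotic. The definition and window should be fixed before outcome data are analysed.

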
#### Analytic approach

We will conduct a comparative interrupted times series (ITS) analysis to examine the relation between the intervention and racial/ethnic differences in sepsis clinical outcomes between AA/B and NHW patients and between LatinX and NHWs. The analysis will be performed separately for our three key outcomes: 1) time to antibiotics, 2) in-hospital mortality, and 30-day readmission and stratified by response to the intervention (change/no change) (Additional File 1; Supplemental Fig. 5). We will consider a pre-exposure to the intervention time beginning 2.5 years (10 quarters) prior to starting the intervention and a postexposure period comprising 2.5 years (10 quarters) following the start of the intervention, with estimates made at every calendar quarter. ITS will be utilized to determine the difference in quarterly rates over time between changers (systems that responded to the intervention) and non-changers, health systems that did not respond to the intervention. Subsequently, ITS allows us to detect if an intervention has impact above and beyond secular trends when randomization is not a feasible option, and is ideal for evaluation of data collected across multiple equally spread time points by testing the changes in the slope of an outcome over time [96]. Additionally, ITS requires at least eight observations pre and post intervention [97]. We will utilize generalized mixed effect models in conjunction with segmented regression to evaluate the effectiveness of our intervention [98]. The model will control for patient-level characteristics, including age, sex, insurance status, Charlson Comorbidity index, and admission through the Emergency Department or transfer from another acute care facility, and hospital-level characteristics including size, academic vs community hospital, number of intensive care beds, annual sepsis case volume. We will also account for seasonality based on calendar quarter by including a “season” term alone and interacted with the treatment indicator and will assess for any residual autocorrelation using autoregressive integrated moving average (ARIMA). To allow a marginal interpretation of results, we will use a linear probability model for all analyses. Because outcomes of patients within a hospital are expected to be correlated, we will account for these non-standard variance–covariance structures by clustering at the hospital level. All coefficients will be modeled as fixed effects.

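### Time to antibiotic is an uncapped mean from hospital arrival, in code-identified admissions with no onset rule and with transfers-in, so a few long intervals can swamp the 30-minute threshold

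*Protocol article*

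**What the plan says.** The section of the protocol article on evaluating racial inequities (Aim 3) defines the outcome as the "difference in mean time from hospital arrival to first antibiotic administration for all AA/B patients and NHW patients", and likewise "between LatinX and NHW patients respectively presenting with sepsis". It continues: "This value will be calculated quarterly. We will use *t-tests* to measure statistically significant differences between AA/B and NHW patients". The threshold is also on the mean scale: "A clinically meaningful difference in mean time to antibiotic would be 30 min". Age and sex standardization is stated for the mortality and readmission rates, but not for this outcome.

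The same section gives one case rule for all outcomes: "We will identify hospital admissions for sepsis using validated International Classification of Diseases, Ninth Revision, Clinical Modification (ICD-9-CM) diagnosis procedure codes", covering infection and organ failure. It was chosen for its sensitivity. No condition on onset or on presence at admission accompanies it. On volume, for each health system, "we expect to be able to observe at least 140 AA/B patients with sepsis each year", and the authors conclude that each outcome can be tracked within each system at each quarter.

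The Analytic approach section gives one covariate list for all three outcomes. It includes "admission through the Emergency Department or transfer from another acute care facility". It then states: "To allow a marginal interpretation of results, we will use a linear probability model for all analyses".

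**The concern.** There are four linked problems, all in what the text fixes rather than in what it omits.

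1. **Population.** The outcome sentence limits the patients to those who present with sepsis. The case rule selects whole admissions by code, and codes alone cannot separate sepsis at arrival from sepsis that begins later in the stay. The rule therefore does not deliver the limit.
2. **Clock.** A transferred patient may have had the first dose before arriving. The interval from arrival to the next recorded dose then says nothing about early identification. An entry-route covariate shifts the mean level for transfers; it does not correct their times or the skew.
3. **Summary measure.** An uncapped mean and a t-test give most weight to the longest intervals, which are the ones least likely to reflect recognition at presentation.
4. **Model.** A linear probability model is for 0/1 outcomes. Prescribing it for every analysis misdescribes a time in minutes.

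At stake is one of the three key clinical outcomes. A gap of the size the authors call meaningful could be lost in the noise from a handful of long intervals.

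**Working it through.** **Inputs from the document.** Over 19,000 inpatient admissions; about 12% AA/B; sepsis in 6% of adult hospitalizations; at least 140 AA/B sepsis cases per system per year; eight systems; 30-minute threshold.

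**The plan's own count.** 19,000 × 0.12 × 0.06 = 136.8 per year. The stated 140 is reached at 140 / 0.0072 = 19,444 admissions, which fits a volume of over 19,000. The figure reproduces. Per quarter: 140 / 4 = 35 per system, and 35 × 8 = 280 with all systems pooled.

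**Excess time that moves the AA/B mean by 30 minutes.** Excess hours = 30 × n / 60.
- One system, n = 35: 17.5 hours. One case 18 hours late gives 18 × 60 / 35 = 31 min; one case 72 hours late gives 72 × 60 / 35 = 123 min.
- Eight systems, n = 280: 140 hours, which is about 6 cases at +24 h, 3 at +48 h or 2 at +72 h.

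Only the hypothetical delays (18 to 72 h) are not from the document.

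**Unequal shares by race (all inputs assumed).** If late-clock cases average h hours, the others average 150 min, and the share of late-clock cases differs by 1 percentage point between racial groups, the gap shifts by 0.01 × (60h − 150): 27.3 min at 48 h, 41.7 min at 72 h, 70.5 min at 120 h.

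**Equal shares in both groups: loss of power.** Assumed: base SD 120 min; a share f = 0.05 delayed by a fixed d minutes; 200 Non-Hispanic White (NHW) cases per system-quarter (19,000 × 0.06 × 0.70 / 4 = 199.5, with a 70% NHW share assumed); two-sided 5% level. SD = √(120² + f(1 − f)d²). The standard error for eight systems is SD × √(1/280 + 1/1600), and power for a true 30-minute gap is Φ(30/SE − 1.96).

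| Delay in 5% of cases | SD (min) | Power, eight systems pooled |
|---|---|---|
| none | 120 | 0.97 |
| 24 h | 336 | 0.28 |
| 48 h | 639 | 0.11 |
| 72 h | 949 | 0.07 |

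In a single system, power is only 0.28 even with no late-clock cases at SD 120.

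**Simulation.** Welch t-tests, 2,000 runs per setting. Assumed: lognormal base with mean 180 and SD 120 min; the same group sizes; late-clock cases given an added exponential delay with mean 72 h.
- True 30-minute gap, pooled, 5% late-clock in both groups: power falls from 0.95 to 0.05 on the raw scale, and from 0.97 to 0.74 on the log scale.
- No true gap, 5% in both groups: an observed gap of at least 30 min appears in 91% of single-system quarters (17% with no late-clock cases) and 73% of pooled quarters (0%). The t-test rejects in about 20% of single-system quarters but only about 7% of pooled ones.
- No true gap, 10% late-clock in AA/B against 5% in NHW, pooled: the raw-scale t-test rejects in 43% and the log-scale test in 55%. A robust scale alone does not cure a racial difference in the share of such cases, so the eligible set has to be fixed as well.

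**The case against.** A reader might infer that the outcome deliberately includes hospital-onset sepsis. The document does not say so. The outcome sentence says presenting with sepsis, while mortality and readmission are worded differently, which is consistent with an intended limit for this outcome alone. An article may also leave the coding detail to the full protocol. This stands as a reading of intent. What remains is that the only case rule given does not achieve the limit, and the two statements need reconciling.

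A reader might also infer that any shift in case mix would bias the intervention effect. It would not. A change over time shared by both racial groups moves both means and leaves the gap alone. A stable racial difference largely drops out of the comparison of change between responding and non-responding systems. Bias there needs a racial difference that changes over time and does so differently by response group, and nothing in the document shows that.

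Three further points against the concern have weight:
- The segmented model adjusts for entry route and case mix, so the unadjusted description applies only to the quarterly differences and t-tests. That transfers are timed for this outcome is itself an inference from the shared covariate list, though a strong one.
- For minutes, the named model would in practice be an ordinary linear model. That is a specification error and not an impossible fit; the harm is sensitivity to skew.
- A mean difference matches the 30-minute threshold, and a median or log analysis would change the estimand. This favours a remedy that stays in minutes.

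**Conclusion.** The concern holds in a limited form. Followed as written, the plan measures early identification by an uncapped, untransformed mean in a set of admissions that its case rule does not confine to sepsis at presentation, with transfers-in included, and it names a model meant for binary outcomes.

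The size that rests on the document's own count is 17.5 excess hours per system-quarter, or 140 hours pooled over eight systems, for a 30-minute shift. The main consequence is lost precision that hides a true gap. False significance needs unequal shares by race or small single-system quarters; with equal shares and pooled data the t-test stays near its nominal level.

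Every share, delay, SD, baseline mean and NHW count above is an assumption, as is the 5% level, which is not stated for Aim 3. The power and simulation figures illustrate the mechanism and do not predict this study's results.

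**What to change.** For time to antibiotic only:

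1. Reconcile the case rule with the outcome sentence: limit it to sepsis present on admission, if that EHR field is available, and exclude inter-hospital transfers-in. Keep the wider cohort for mortality and readmission.
2. Replace the raw-mean t-tests with a continuous-outcome segmented model that is robust to skew. A restricted mean with a pre-specified cap keeps the 30-minute scale; median or log-time regression can serve as a sensitivity analysis.
3. Confine the linear probability model to mortality and readmission.

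The cost is mainly wording. Transfer status is already a planned covariate; whether the sites hold a present-on-admission field is not stated and must be checked. The downsides are a smaller sample for this outcome and, with a cap, a slightly different estimand.

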**Support services:**
• Discharge planning
• Manager in charge of financial counseling/uncompensated care
• Post discharge rehab facilities (residential and OPT)

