#### Intervention components

Based on our prior success in similar organizational change efforts [29], the 2.5 year intervention will include three components: 1) a series of five semiannual virtual, cross-site forums attended by four key members of each Guiding Coalition; 2) a series of four one-day workshops onsite with the full coalition at each hospital; and 3) a web-based platform to allow sites to share experiences and to serve as a repository for program resources. The content will build on and extend the previously published LSL curriculum [29]. *Semiannual forums* will bring sites together as a learning community for advice and problem solving on culture change to address structural racism in sepsis care. The sequence of forums will move sites from understanding and ‘buying in’ to the evidence base to sharing implementation challenges and successes. In the annual and closing forums, sites will vote for the “STAR” (Striving to Achieve the Remarkable) site that best exemplifies commitment to the objectives of the learning community, a highly motivational activity in LSL. *On site workshops* will build leadership capacity within the full Guiding Coalition to mitigate structural racism as it manifests in sepsis care. Each of the four workshops will include one full day of content, scheduled based on site preferences. The core curriculum for the workshops will incude both *how to work* (improving the domains of organizational culture that are required to mitigate structural racism and the underlying ecological barriers to health equity) and *what to work on* (strategic problem solving [52] to address root causes of inequities in sepsis care and outcomes in their site, see Additional File 1; Supplemental Fig. 2 for examples). In the first workshop, we will orient Guiding Coalition members to the intervention and the evidence base, promote reflection on their own measures of inequities in sepsis care and baseline organizational culture (survey measure described below), and name a problem statement and objective on which the group will focus their root cause analysis process. We will also invest in effective working relationships and processes among coalition members, including representation and role clarity [58], decision-making [59], and accountability [60]. Between workshops, the coalitions will be tasked with making and measuring progress toward addressing identified priority root causes of racial inequities in sepsis care in their home systems. At subsequent workshops, members will report on their progress, with the goal of solving implementation challenges and further developing their individual and group capacity for adaptive leadership [25, 26]. Additional workshop content will include diagnosing and shaping organizational culture, engaging conflict productively [61], using levels of analysis to diagnose organizational challenges [62, 63], and working with power and hierarchy [64, 65]. Content will be tailored to the local context by adjusting the timing of these modules to meet teams’ most pressing needs, adapting the specific examples and experiential learning exercises used in each module, articulating linkages between these content areas and ongoing work in each site, and encouraging each site to focus on root causes of inequities in sepsis care and treatment that are most salient in their environment. The facilitation team will include expert facilitators from across the United States, with backgrounds in organizational development, leadership education, anti-racist organizational change, and clinical quality improvement; most facilitators will be drawn from a faculty pool with deep experience developed through prior successful projects. Facilitators will work in teams of two or three, including a lead facilitator and additional experts tailored to the needs of each site. To promote standardization across sites while allowing for adaptation to local context, facilitators will use a fidelity checklist for each workshop. At the end of each workshop, the lead facilitator will prepare a structured written summary of decisions and action items for report back to the Guiding Coalition and to the full facilitation team. Between workshops, *a web-based information sharing platform* will serve two primary functions: (1) to serve as an accessible, up-to-date repository of project materials and references and (2) to support direct communication across hospital teams for sharing of successes, barriers, and project updates.

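### In-hospital mortality stops counting at discharge, so a post-launch change in length of stay or hospice discharge could narrow the racial gap with survival unchanged

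*Protocol article*

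**What the plan says.** The Aim 3 section takes mortality from hospital EHR data. The plan is to "determine the difference in quarterly in-hospital mortality rate by 30 days" for AA/B against NHW and for LatinX against NHW patients admitted for sepsis. Rates are standardized by age and sex. On size, the section says: "A clinically meaningful difference in rates of in-hospital mortality would be greater than 1" per cent.

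The background section on evidence of structural racism lists, for AA/B and LatinX patients, lower intensity of care, with the examples "less likely to receive ICU care, longer length of stay, less frequent referral for follow-up care". It attaches no figure to the difference in stay.

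Under support services, the sample coalition membership table lists "Discharge planning" and post-discharge rehabilitation facilities. Neither carries the mark for core members. The intervention section leaves the topic to the sites, "encouraging each site to focus on root causes of inequities in sepsis care and treatment that are most salient in their environment".

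The Analytic approach section compares changer with non-changer systems over 10 quarters before and 10 after the start. The patient covariates are age, sex, insurance, Charlson index and route of admission. The hospital covariates are size, academic status, intensive care beds and sepsis volume. None concerns when or to where a patient is discharged, and the limitations in the Discussion do not raise it.

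**The concern.** In-hospital death depends on two things: whether the patient dies, and whether the death comes before discharge. The second depends on discharge practice. The article itself says that stay differs between the groups being compared, so the groups are observed for death over different lengths of time.

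That matters if the difference moves during the study. Suppose stays of AA/B or LatinX patients shorten towards those of NHW patients after launch, or more dying patients in these groups are discharged to hospice. Some deaths then fall outside the outcome, and the gap narrows without any death prevented. If stays lengthen instead, a real improvement could be hidden. The segmented model would attribute either change to the intervention, since it coincides with launch. At stake is whether a narrowed gap can be read as better survival.

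**Working it through.** **The plan's own figure.** The only reproducible number in the Aim 3 outcome text is the case volume: 19,000 × 0.12 × 0.06 = 136.8 AA/B sepsis patients per system per year, against at least 140 stated. It reproduces, since volumes are given as over 19,000 (19,444 gives 140). At 140 / 4 = 35 patients per quarter, 1 point of mortality is 0.35 deaths per system and quarter. A shift of that size would not be noticed from quarterly counts.

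**Inputs.** From the article: the outcome definition, the 1% threshold (read here as 1 percentage point), and the direction of the difference in stay. Assumed, because the article gives no figures: 30-day mortality, mean stay and the timing of deaths.

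**Step 1: how many deaths must move past discharge.** Let M be 30-day mortality in any setting and s the share of those deaths that occur before discharge.

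In-hospital rate = M × s. Share of deaths to move for 1 point = 0.01 / M.

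| M | Share of deaths to move |
|---|---|
| 10% | 10% |
| 15% | 6.7% |
| 20% | 5% |
| 25% | 4% |
| 30% | 3.3% |

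For example, with M = 20% and s falling from 0.80 to 0.75, the rate falls by 0.20 × 0.05 = 1.0 point.

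**Step 2: what change in stay would do that.** This was simulated with 1,000,000 patients and fixed death times. Death times follow an exponential distribution truncated at 30 days, with scale 8 or 12 days. Stay follows a gamma distribution with shape 2, independent of death time. Only mean stay changes, so 30-day mortality is the same throughout. Rates are in-hospital mortality in per cent; changes are in points.

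| M | Death-time scale | Stay 10 d | Stay 9 d | Stay 8 d | 10 to 8 d | 9 to 8 d |
|---|---|---|---|---|---|---|
| 15% | 8 d | 9.55 | 9.08 | 8.53 | 1.02 | 0.55 |
| 15% | 12 d | 8.18 | 7.70 | 7.16 | 1.02 | 0.54 |
| 20% | 8 d | 12.69 | 12.06 | 11.35 | 1.34 | 0.71 |
| 20% | 12 d | 10.92 | 10.25 | 9.52 | 1.40 | 0.73 |
| 25% | 8 d | 15.92 | 15.12 | 14.25 | 1.67 | 0.87 |
| 25% | 12 d | 13.72 | 12.88 | 11.97 | 1.75 | 0.91 |

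A two-day cut in one group moves its rate, and so the gap, by 1.0 to 1.8 points. A one-day cut moves it by 0.5 to 0.9.

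**Step 3: what reaches the planned contrast.**

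Spurious effect = shift in the gap in changers − shift in the gap in non-changers.

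A constant difference in stay contributes zero, and equal drift in both sets of systems cancels. The step 2 figures apply in full only if the change occurs in changers alone.

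**Scale.** In the prior study described in the article, 30-day risk-standardized mortality fell by 1.07 points in hospitals with culture change and by 0.23 in the others, a contrast of 0.84. The artefact can be as large as that.

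**The case against.** The outcome is labelled openly as in-hospital mortality, and it is a practical choice for a hospital EHR source. A stable racial difference in stay is absorbed by the pre-period, so bias needs a differential change after launch. Both points stand, and the concern is limited accordingly.

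The sizes rest on assumptions. The article mentions longer stay only in a list of examples, and a one-day cut stays below the threshold. The simulation makes stay independent of death time. If patients discharged earlier are mainly those at low risk, the shift is smaller; if dying patients leave for hospice, it may be larger. Neither can be settled from the article.

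A reader might infer that the coalitions are set to work on discharge. The article does not say so: the membership table is a sample, the discharge roles are not core, and sites choose their own focus. A shift in discharge is possible but not planned.

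A reader might also infer that readmission is compromised, because it is described for "LatinX and NHW patients with an index hospitalization for sepsis" and patients who die in hospital cannot be readmitted. The wording is silent on whether only live discharges count, and an article may leave that to the full protocol. The effect is also small. In the same simulation, with an assumed 20% readmission risk, cutting stay from 10 to 8 days moves readmission over all index stays by 0.05 to 0.12 points, and among live discharges by 0.13 to 0.25 in the other direction. The plan's yardstick reads: "A clinically meaningful difference in rates of 30-day readmission would be 5" per cent. That reading is not supported.

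**Conclusion.** The point holds for mortality alone, and conditionally. The outcome ends at discharge, the article reports that stay differs by group, and nothing in the standardization, covariates or stated limitations deals with discharge timing. If the gap in stay or hospice discharge changes more in changer systems after launch, the in-hospital mortality gap can move by about 0.5 to 1.8 points with survival unchanged, against a threshold of 1 point. The range assumes 30-day mortality of 15-25%, a mean stay cut from 9 or 10 to 8 days in one group, the death-time distributions above, and a change confined to changer systems. This does not invalidate in-hospital mortality as the outcome. It means that a narrowed gap, shown alone, cannot be told apart from a changed discharge pattern.

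**What to change.** Keep in-hospital mortality as the outcome and add two analyses from the same EHR source:

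- A sensitivity ITS, with the same model and the same changer/non-changer contrast, on in-hospital death or discharge to hospice within 30 days of admission. Add post-discharge deaths where the EHR records them.
- The same ITS on length of stay and on discharge destination, by racial/ethnic group.

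State in advance that a narrowed in-hospital mortality gap will be interpreted as reduced mortality only with these results beside it, and with caution if stay or hospice discharge shifted at the same time. Adding length of stay to the mortality model as a covariate is no substitute, because stay is cut short by death and may itself respond to the intervention.

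The cost is a few sentences of wording and a little more analysis. The limits should be stated too. Hospice discharge is a proxy for death. Deaths outside the system are only partly recorded, and capture may differ between groups or over time. For that reason the mortality claim should not be made to depend formally on recorded post-discharge deaths.
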